#### Adverse reaction rate

2.6.2

Including any uncomfortable symptoms (such as dizziness, nausea, etc) during treatment.

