**Methods::**

This is a prospective randomized controlled trial. 272 patients with myocardial infarction will be randomly divided into an experimental group and a control group according to 1:1, with 136 cases in each group. The control group: conventional treatment; the experimental group: increase Tai Chi exercise on the basis of the control group. Both groups will receive standard treatment for 24 weeks and will be followed up for 3 months. Observation indicators include: total effective rate, 6 minutes walking test, brain natriuretic peptide, left ventricular ejection fraction, the adverse reaction rate, etc. The data will be analyzed by using SPSS 25.0 software.

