### Interventions

2.5

This study will select patients who meet the criteria of this study by recruiting in the hospital. A randomized controlled study will be used, in which the control group: conventional treatment; the experimental group: Tai Chi exercise will be added to the control group. The 2 groups of patients will receive the same routine care. During the trial period, avoid smoking, alcohol and irritating food, avoid strenuous exercise, and pay attention to adverse reactions. When necessary, the attending doctor can appropriately adjust the plan according to the patient's condition, and all intervention methods will be recorded in detail for the final result analysis. Efficacy assessors are not aware of the study group plan, and data statisticians are not involved in the design and implementation of the study. Before and after treatment, the health status of each patient will be evaluated, including the outcome indicators, and all patients will be followed up by telephone. Follow-up content includes cardiovascular events and rehospitalization.

Control group: according to the relevant guidelines after myocardial infarction intervention, standard drug treatments will be given, including antiplatelet drugs, statins, angiotensin converting enzyme inhibitors, nitrates, β-receptor blockers, and health education. The content of the education includes the control of myocardial infarction risk factors, techniques for improving sleep quality, diet guidance, etc, and pays attention to communicating with patients, mastering their psychological and emotional changes, and avoiding or alleviating bad moods such as anxiety and depression in elderly patients.

Experimental group: on the basis of conventional treatment, the experimental group will be given 24 simplified Tai Chi. Professional Tai Chi teachers will teach and practice the subjects to ensure that the practice time and movement rhythm are basically the same. The whole set of Tai Chi includes 3 parts: preparation activity, training activity and end activity, totaling about 20 minutes, twice a day, once in the morning and once in the afternoon, and lasts for 24 weeks.

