### Statistical analysis plan

2.9

The database is established by Excel. The full analysis set refers to the intent-to-treat analysis of all subjects randomly enroll, treat at least once and visit at least once. Per-protocol set: includes all subjects who comply with the trial protocol, have no missing baseline variables, and can measure the main variables. safety set: including random enrollment, at least 1 medication, and at least 1 safety visit after medication.

In this study, SPSS25.0 statistical analysis software will be used for data analysis. If the measurement data meet the normal distribution, the independent sample *t* test is used between the groups, and the paired sample *t* test is used within the group. The results are represented by ($\bar{X}\pm S$); Nonparametric test will be used for those who did not meet the normality, and the results will be expressed in quartiles; Chi square test will be used for counting data. The incidence of adverse events will be compared by chi square test. *P* *<* *.05*, with statistical significance.

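### The only stated between-arm safety rate counts any symptom, which dilutes exercise-type harm by an amount that depends on a background rate the protocol does not give

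*Protocol article*

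**What the plan says.** Section 2.6.2 gives the content of the adverse reaction rate in one sentence: "Including any uncomfortable symptoms (such as dizziness, nausea, etc) during treatment". It sets no severity threshold, asks for no relation to the exercise, and has no category for exercise-type events. Section 2.9 fixes the comparison: "The incidence of adverse events will be compared by chi square test", at the 5% level.

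Under section 2.5, in the control group "standard drug treatments will be given, including antiplatelet drugs, statins, angiotensin converting enzyme inhibitors, nitrates, β-receptor blockers", together with health education. The other arm builds on this: "on the basis of conventional treatment, the experimental group will be given 24 simplified Tai Chi", "totaling about 20 minutes, twice a day, once in the morning and once in the afternoon, and lasts for 24 weeks". Tai Chi is therefore the only planned difference between the arms.

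The article has other safety provisions. Section 2.8 provides for safety monitoring of each participant, review of all adverse events with a ruling on causality, and a DSMB. Section 2.5 lists cardiovascular events and rehospitalization as content of the telephone follow-up. The Introduction and the Discussion both name safety as something the trial is to evaluate.

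**The concern.** The treatment under study is an exercise, so the harms it could add are events such as falls, musculoskeletal injury or symptoms on exertion. The rate in section 2.6.2 counts these together with every other discomfort over 24 weeks. The two examples given, dizziness and nausea, are complaints that patients in either arm could report, since both arms have had an infarction and take several drugs.

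In a patient-level any-symptom rate, someone already counted for an unrelated symptom adds nothing when an exercise injury follows. The difference between arms shrinks, and the shared symptoms add variance. Equal questioning in the two arms would not cure this, because it comes from the definition of the outcome. The conclusion on safety is at stake; the primary efficacy result is not affected.

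**Working it through.** **The plan's own figure.** The article gives no expected rate, detectable difference or power for adverse reactions. Its one sample-size calculation (section 2.4) concerns the total effective rate, and it reproduces:

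- n = 0.8 × 0.2 × [(1.64 + 1.28)/0.15]² × 2 = 121.26, rounded up to 122 per arm.
- 122/0.9 = 135.6, rounded up to 136 per arm, 272 in total.

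**Inputs from the article.** 136 per arm; chi-square test at 5%, taken as two-sided and without continuity correction because the article states neither.

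**Assumed inputs, absent from the article.** Risk of exercise-type harm h: 1% in controls and 8% with Tai Chi. Background risk b of any other symptom: the same in both arms, independent of the harm, and varied over a range.

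**Formulas.** The pooled any-symptom risk in an arm is p = b + (1 − b)h. The difference between arms is therefore (1 − b) × (0.08 − 0.01) = 0.07(1 − b). Power is the exact binomial probability that z exceeds 1.96 in the direction of harm, where z is the difference in proportions divided by √[p̄(1 − p̄) × 2/136] and p̄ is the mean of the two proportions.

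**Two cases by hand.**

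- b = 0: 1% versus 8%, p̄ = 0.045, standard error √(0.045 × 0.955 × 2/136) = 0.0251, expected z = 0.07/0.0251 = 2.8.
- b = 20%: 20.8% versus 26.4%, p̄ = 0.236, standard error √(0.236 × 0.764 × 2/136) = 0.0515, expected z = 0.056/0.0515 = 1.1.

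The difference falls by a fifth while the standard error doubles. At moderate background rates, most of the loss comes from added variance.

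**Exact power, 136 per arm, harm 1% versus 8%.**

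| Background b | Control | Tai Chi | Power |
|---|---|---|---|
| 0 (harm counted alone) | 1.0% | 8.0% | 85% |
| 2% | 3.0% | 9.8% | 66% |
| 5% | 6.0% | 12.6% | 48% |
| 10% | 10.9% | 17.2% | 32% |
| 20% | 20.8% | 26.4% | 19% |
| 40% | 40.6% | 44.8% | 10% |

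With 122 per arm, power is 80% for harm alone and 44%, 18% and 9% at backgrounds of 5%, 20% and 40%.

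**Sensitivity to the harm assumption.**

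- If events on a harm list also occur in controls, 5% versus 12%, power is about 56% with the list counted alone.
- If the harm is smaller, 1% versus 5%, power is 49% counted alone.
- If Tai Chi adds a 10% risk absent from controls, the any-symptom test keeps about 78% power at a 5% background, but only 23% at 30%.

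**The case against.** The strongest objection concerns what the text fixes. Section 2.6.2 can be read as the scope of what is recorded, and the chi-square sentence in section 2.9 would also fit a comparison by type of event. Nothing says outright that all symptoms collapse into one yes/no per patient. This is a condensed article, and detailed tabulation of events can sit in a fuller document. That is fair, and the point is therefore tied to the natural reading of the words, an outcome named as a single rate. It is not a complaint that a table is missing.

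Second, the pooled test is not the only safety information. The causality ruling, the DSMB and the recording of cardiovascular events could each bring a harm to light. This stands. However, the article does not say that the causality ruling restricts what enters the adverse reaction rate or its test, and cardiovascular events and rehospitalization do not cover falls or musculoskeletal injury.

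Third, a reader might infer that shared symptoms swamp the harms of Tai Chi and leave the trial almost blind to them. The document does not support this, because it gives no background symptom rate. At 2% or 5% the test is weakened, not blind, and a large harm is still usually found. A reader might also infer that the plan will treat a non-significant result as proof of safety; no section says so.

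Fourth, the arm size was set for the primary outcome. It limits detection of small harms however they are counted, as the 49% for 1% versus 5% shows. This stands too, and it limits what the added comparison can deliver.

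**Conclusion.** The concern holds in a conditional form. Read naturally as one any-symptom rate, the stated safety outcome dilutes exercise-type harm in a trial where the exercise is the only difference between arms. For an assumed harm of 1% versus 8%, power falls from about 85% counted alone to 66% at a 2% background, 32% at 10% and 10% at 40%. The direction follows from the definition. The size rests on assumed harm and background rates and on their independence, none of which the article gives. The gain from counting exercise-type harm separately is smaller when the listed events also occur in controls. The other safety provisions reduce the consequence but do not change what this rate measures. The point bears on the safety conclusion and is worth acting on because the remedy is cheap.

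**What to change.** - Keep the any-symptom rate and its chi-square test as they stand.
- Add a prespecified between-arm comparison of the proportion of patients with at least one exercise-type harm, for example falls, musculoskeletal injury or exertional symptoms. Report a risk difference with a confidence interval, so that the size of harm not excluded is visible.
- Ask about these events with the same questions in both arms at the 12- and 24-week assessments already scheduled in section 2.7.
- State that a non-significant any-symptom test will not be read as evidence that Tai Chi is safe.

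The cost is one checklist on the assessment form and one table. The small downside is that the event list has to be agreed in advance. No treatment or clinical rule changes.

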### Sample collection

2.7

Data will be collected according to the evaluation criteria before the start of treatment, 12 weeks after the treatment, and at the end of 24 weeks of treatment. After the treatment, each patient will be followed up by telephone for 3 months. Detailed follow-up information can not be collected and the reasons for loss to follow-up will be recorded. Access to the database is limited to the researchers of this research group.

### Study quality control

2.8

Throughout the experiment, each participant will be monitored for safety. All adverse events will be transferred to the clinical trial institution ethics committee of the office, who will review the event and rule on causality. We set up a Data and Safety Monitoring Board (DSMB). Members of DSMB include physicians, clinical pharmacists, test method experts, statistical experts, and members of the ethics committee, who will conduct a risk assessment and safety analysis procedures based on termination conditions.

### Statistical analysis plan

2.9

The database is established by Excel. The full analysis set refers to the intent-to-treat analysis of all subjects randomly enroll, treat at least once and visit at least once. Per-protocol set: includes all subjects who comply with the trial protocol, have no missing baseline variables, and can measure the main variables. safety set: including random enrollment, at least 1 medication, and at least 1 safety visit after medication.

In this study, SPSS25.0 statistical analysis software will be used for data analysis. If the measurement data meet the normal distribution, the independent sample *t* test is used between the groups, and the paired sample *t* test is used within the group. The results are represented by ($\bar{X}\pm S$); Nonparametric test will be used for those who did not meet the normality, and the results will be expressed in quartiles; Chi square test will be used for counting data. The incidence of adverse events will be compared by chi square test. *P* *<* *.05*, with statistical significance.

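### The safety set is defined by medication and a later safety visit, so it does not register exposure to Tai Chi and leaves out harmed patients who never reach such a visit

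*Protocol article*

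**What the plan says.** Section 2.9 (Statistical analysis plan) sets out three analysis sets. The one for harms is the "safety set: including random enrollment, at least 1 medication, and at least 1 safety visit after medication". In the same paragraph the full analysis set uses a different exposure term: "all subjects randomly enroll, treat at least once and visit at least once".

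Section 2.5 (Interventions) describes what the arms receive. For controls, "standard drug treatments will be given, including antiplatelet drugs, statins, angiotensin converting enzyme inhibitors, nitrates, β-receptor blockers, and health education". For the other arm, "on the basis of conventional treatment, the experimental group will be given 24 simplified Tai Chi". No study drug is tested.

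On when and how harms are captured:
- Section 2.7 (Sample collection) schedules data collection "before the start of treatment, 12 weeks after the treatment, and at the end of 24 weeks of treatment", followed by three months of telephone follow-up.
- Section 2.5 says that the telephone follow-up covers cardiovascular events and rehospitalisation.
- Section 2.8 (Study quality control) says "Throughout the experiment, each participant will be monitored for safety".
- Section 2.6.2 describes the safety outcome: "Including any uncomfortable symptoms (such as dizziness, nausea, etc) during treatment".

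No section of the article defines a safety visit.

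**The concern.** A safety set should hold the people who could have been harmed by what is being tested. Whether a patient belongs to it should not depend on how that patient fared afterwards. The written definition falls short on both counts.

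- **Exposure.** The criterion names a treatment that both arms share. It neither identifies patients who practised Tai Chi nor starts the clock at a first session.
- **Selection on outcome.** Requiring a later visit means that a patient whose harm prevents any such visit is not counted.

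The article gives the evaluation of efficacy and safety as its purpose (Introduction and Discussion). What is at stake is the adverse event comparison, not the primary endpoint.

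**Working it through.** This is a point about a definition, so most of the check is setting the sections side by side. The arithmetic only illustrates direction.

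**1. Arm size used in the illustration (section 2.4).** The plan's own figure reproduces: 0.8 × 0.2 × ((1.64 + 1.28)/0.15)² × 2 = 121.26, rounded up to 122 per arm. Allowing for 10% dropout, 122/0.9 = 135.6, rounded up to 136 per arm and 272 in total. The point does not depend on this figure.

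**2. Who meets the medication condition.** By section 2.5, controls get standard drugs and the Tai Chi arm gets the same conventional treatment plus Tai Chi. Three cases show what the condition does:

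| Patient | Took background drugs | Did Tai Chi | Meets the condition |
|---|---|---|---|
| Control | yes | not assigned | yes |
| Tai Chi arm, practised | yes | yes | yes |
| Tai Chi arm, never practised | yes | no | yes |

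The last two rows are treated alike, so the condition does not separate exposed from unexposed patients. The interval that begins after medication also need not coincide with the first Tai Chi session.

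**3. Who fails the visit condition.** Again by cases:
- Harmed early, then attends at least one later safety visit: stays in, and the event counts.
- Harmed, then dies or withdraws with no later safety visit: leaves the set, and the event leaves with the patient.
- Not harmed, no later safety visit: leaves the set, and only the denominator changes.

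The number of events in the set can therefore fall below the number that occurred and can never exceed it.

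**4. Illustration with assumed numbers.** The documents give neither an adverse event rate nor a count of patients without a visit. Suppose that 14 of 136 patients in one arm have an adverse event (14/136 = 10.3%) and that k of those 14 have no later safety visit. The rate in the safety set is (14 − k)/(136 − k):

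| k | Events / patients in set | Rate |
|---|---|---|
| 0 | 14/136 | 10.3% |
| 1 | 13/135 | 9.6% |
| 3 | 11/133 | 8.3% |
| 5 | 9/131 | 6.9% |
| 7 | 7/129 | 5.4% |

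Losing harmed patients lowers the observed rate in the arm that loses them. The effect on the difference between arms depends on how many are lost from each, which cannot be known in advance.

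**5. Does another section repair it?** Section 2.8 provides for monitoring throughout, with adverse events passed to the ethics committee. That governs collection and review, and does not change who is in the analysis set. The second exclusion list in section 2.3 covers enrolled patients whose data are left out of the final analysis. It includes severe adverse events and withdrawal for any reason, and section 2.9 does not exempt the safety set from it. Nothing in the article restores the lost patients.

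**The case against.** **Loose wording.** The full analysis set in the same paragraph speaks of treatment, so medication may simply be a slip for it. That is plausible, but it is not what is written. Conventional treatment is also given to both arms, so the word treatment alone would still not refer to Tai Chi. And a change of word would leave the visit condition in place.

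**How many patients are lost.** A reader might infer that everyone harmed before a first visit is dropped. The text asks only for at least one later visit, so a patient harmed in week 2 who attends at week 12 stays in. A reader might also infer that week 12 is the first possible safety visit. It is the first scheduled post-baseline data collection in section 2.7, but safety visits are not defined. An earlier or unscheduled contact might qualify, and a condensed article may leave that schedule to the full protocol. This stands, and it limits the loss to patients who never have such a visit.

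**Oversight continues.** Adverse events go to the ethics committee and there is a Data and Safety Monitoring Board. This also stands: the definition does not hide events from those bodies. What it affects is the comparison between arms.

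**The test.** Section 2.9 says "The incidence of adverse events will be compared by chi square test", and a reader might infer that its P values are wrong at low counts. With 136 per arm, 0 v 5 events gives P = 0.024 by Pearson's test and 0.060 by Fisher's; 1 v 7 gives 0.031 and 0.066. The gap does not show Pearson's test to be wrong, because Fisher's test is conservative. Enumerating all tables at 136 per arm, with equal true event rates of 1%, 2%, 3% and 5%, the actual two-sided size at nominal 5% is 2.5%, 4.5%, 4.4% and 4.8% for uncorrected Pearson. For Fisher it is 0.1%, 1.0%, 1.7% and 2.3%. Pearson's test stays below 5% throughout, and a switch to Fisher's would make harm harder to detect. The choice of test is therefore no part of this point.

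**The exclusions in section 2.3** are a separate matter. They matter here only because section 2.9 does not say whether they reach the safety set.

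**Conclusion.** The point holds in a limited form. As written, the safety set admits nearly every randomised patient on a criterion unrelated to the tested intervention, and it leaves out harmed patients with no later safety visit. The second feature can only remove events. Its size cannot be computed from the documents, and the figures above rest on an assumed 14 events in 136 patients.

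The conclusion takes the definition literally and assumes that the full protocol does not define it differently. If any contact, including a telephone call or a hospital report, counts as a safety visit, fewer patients are lost, but the article does not say so. The definition should be corrected because it bears on a stated aim and the correction is cheap. The primary efficacy analysis is not affected.

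**What to change.** In section 2.9:

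1. Delete the post-baseline visit condition from the safety set.
2. Replace medication with the assigned intervention. Make the main adverse event analysis one of all randomised patients by assigned arm.
3. Count events from randomisation by any route of report, including the telephone follow-up in sections 2.5 and 2.7 and the monitoring in section 2.8.
4. Add a supplementary table restricted to Tai Chi patients with at least one session, so that harm under actual exposure can be read separately.
5. State that the post-randomisation exclusions in section 2.3 do not apply to the safety set.

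The chi-square test can stay.

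The cost is a few lines of text and slightly more analysis of data already planned for collection. One limitation remains: the main safety table will still include some Tai Chi patients who never practised. All-randomised analysis does not remove that dilution, so the supplementary table is needed alongside it.

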#### Efficacy indicators

2.6.1

Main efficacy indicators: total effective rate: referring to the “Guiding Principles for Clinical Research of New Chinese Medicines”,^[13]^ total effective rate = (marked effective number + effective number)/total number × 100%. According to NYHA grading method, evaluate the curative effect of cardiac function: ① Marked effective: cardiac function improved by more than grade 2; ② Effective: cardiac function improved by grade 1, but not as good as grade 2; ③ Ineffective: cardiac function improved less than grade 1; ④ Deterioration: the deterioration of heart function is less than grade 1.

Secondary efficacy indicators: 6 minutes walking test, brain natriuretic peptide, left ventricular ejection fraction, medical outcomes study short-form36 (SF-36).

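### Between-arm tests without baseline adjustment give up precision at no saving, and within-arm paired tests carry the same P<.05

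*Protocol article*

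**What the plan says.** Section 2.7 of the protocol article collects data "before the start of treatment, 12 weeks after the treatment, and at the end of 24 weeks of treatment"; I read the middle time as week 12 of treatment.

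Section 2.9 fixes the tests. For normally distributed measurements, an independent-sample t "test is used between the groups, and the paired sample" t "test is used within the group". Otherwise, "Nonparametric test will be used for those who did not meet the normality". For categorical outcomes, "Chi square test will be used for counting data". One threshold, P<.05, is given for all of these. No covariate or stratification factor is named. The section does not say whether the between-group test is on follow-up values or on changes, or at which visit.

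The primary outcome (section 2.6.1) is a response rate built on change in NYHA grade. The lowest qualifying category reads: "Effective: cardiac function improved by grade 1, but not as good as grade 2". The secondary efficacy outcomes are the 6-minute walking test (6MWT), BNP, LVEF and SF-36. Section 2.3 enrols NYHA classes I to III. Section 2.4 randomises 1:1 with no stratification factor.

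**The concern.** Three features work against the trial.

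- **Continuous outcomes.** The baseline value usually predicts the follow-up value. A t or rank test that does not adjust for it leaves that predictable variation in the error term.
- **Primary outcome.** Response means gaining at least one NYHA grade. A class I patient has no better grade to move to, so baseline class strongly determines who can respond. An unstratified chi-square counts that variation as noise.
- **Within-arm paired tests.** A before-after change in one arm does not estimate the effect of Tai Chi. The plan's own sizing expects most control patients to respond. With a rate of 0.8 and a difference of 0.15, the control rate is 0.8 - 0.075 = 72.5%, 80%, or 0.8 - 0.15 = 65%, according to whether 0.8 is the average, control or experimental rate. Paired tests at the same threshold, not marked as descriptive, leave room to read a significant change in one arm only as a difference between arms.

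At stake are power that the collected data could supply and the clarity of the efficacy conclusion.

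**Working it through.** **Inputs from the protocol article.** Rate 0.8, difference 0.15, normal quantiles 1.64 and 1.28, allocation ratio 1, dropout about 10% (section 2.4); visits (2.7); tests and threshold (2.9); NYHA I to III (2.3).

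**Assumed, because not given.** Correlation r between baseline and follow-up; equal SD at both times; share of patients in class I; response rates by class; two-sided testing at 0.05 (section 2.9 does not state sidedness).

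**Step 1: the plan's own figure.** n = 0.8 × 0.2 × [(1.64 + 1.28)/0.15]² × 2 = 121.26, rounded up to 122 per arm. 122/0.9 = 135.6, so 136 per arm and 272 in total. This reproduces, so the point does not rest on an arithmetic error.

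**Step 2: continuous outcomes, 122 per arm.** Relative to a follow-up-only t test with variance 1, ANCOVA has variance 1 - r² and a change-score t test 2(1 - r). The ratios to ANCOVA are therefore 1/(1 - r²) and 2(1 - r)/(1 - r²) = 2/(1 + r).

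For illustration, take the difference at which the follow-up-only t test has 80% power: (1.96 + 0.84) × √(2/122) = 0.36 SD.

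| r | Follow-up t vs ANCOVA variance | Change t vs ANCOVA variance | Power, follow-up t | Power, change t | Power, ANCOVA |
|---|---|---|---|---|---|
| 0.3 | 1.10 | 1.54 | 80% | 66% | 84% |
| 0.5 | 1.33 | 1.33 | 80% | 80% | 90% |
| 0.7 | 1.96 | 1.18 | 80% | 95% | 98% |
| 0.8 | 2.78 | 1.11 | 80% | 99% | >99% |

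ANCOVA is the most precise for every r strictly between 0 and 1, whichever test the plan intends.

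**Step 3: within-arm paired tests.** Give both arms the same true change, so that Tai Chi has no effect. The standard error of an arm's mean change is √(2(1 - r)/122) SD. If p is the chance that one arm is significant, the chance that exactly one of the two is significant is 2p(1 - p).

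| True change in both arms | r = 0.5: p | r = 0.5: exactly one | r = 0.7: p | r = 0.7: exactly one |
|---|---|---|---|---|
| 0.10 SD | 20% | 32% | 30% | 42% |
| 0.15 SD | 38% | 47% | 57% | 49% |
| 0.20 SD | 60% | 48% | 81% | 30% |
| 0.30 SD | 91% | 16% | 99% | 2% |

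For changes of 0.10 to 0.20 SD, a split result arises by chance about 30% to 49% of the time, against 5% for a between-arm test. For larger changes both arms tend to be significant, which again says nothing about a difference.

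**Step 4: primary outcome.** Simulation of 10,000 trials per scenario with 122 per arm. Response is 72% vs 88% in classes II and III (close to 0.8 ± 0.075) and nil in class I. The remaining patients are split 60:40 between classes II and III.

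| Share in class I | Overall response, control vs Tai Chi | Chi-square power | Stratified (Mantel-Haenszel) power |
|---|---|---|---|
| 0% | 72.0% vs 88.0% | 90% | 89% |
| 10% | 64.8% vs 79.2% | 71% | 85% |
| 20% | 57.6% vs 70.4% | 56% | 81% |
| 30% | 50.4% vs 61.6% | 41% | 75% |
| 40% | 43.2% vs 52.8% | 32% | 69% |

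Hand check at 20%:
- Chi-square: 0.128/√(2 × 0.64 × 0.36/122) = 2.08, power Φ(2.08 - 1.96) ≈ 55%.
- Stratified, where only 0.8 × 122 = 97.6 per arm are informative: 0.16/√(2 × 0.8 × 0.2/97.6) = 2.79, power Φ(0.83) ≈ 80%.

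With equal response in both arms, the chi-square rejected in 4.5% to 5.2% of simulated trials and the stratified test in about 4.6% to 5.3%.

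**The case against.** The strongest reply is that nothing here is invalid. Under randomisation the unadjusted tests are sound, the estimates are unbiased, and their standard errors already allow for chance imbalance. That stands. A reader might infer bias or a raised false-positive rate, and neither the design nor the simulation supports that.

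Second, a reader might quote a gain worth 96% more patients (r = 0.7). That holds only if follow-up values are tested. Section 2.9 does not say so, and if changes are tested the gain at that r is 18%. Both cases must be shown. The 80% starting power is also illustrative, because section 2.4 sizes the trial on the binary primary alone.

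Third, it would be too strong to say that the primary ignores baseline, since response is itself a change in NYHA grade. What is unaccounted for is baseline class. Much of the power loss in Step 4 comes from enrolling patients who cannot respond, and no test restores the diluted difference. Stratification only removes the noise they add.

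Fourth, the plan nowhere says that a within-arm result will support efficacy. That is also right: the plan leaves the misreading open but does not commit to it.

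Finally, a repeated-measures model, a log scale for BNP, and objections to choosing tests by a normality check are preferences or detail that a fuller analysis plan may settle. They are not part of this point.

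**Conclusion.** The point holds as a matter of efficiency and interpretation, not validity. Section 2.9 affirmatively names tests that are less precise than the collected data allow.

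For continuous outcomes the direction is certain for any correlation strictly between 0 and 1. At r = 0.5 either unadjusted t test has 1.33 times the ANCOVA variance; at r = 0.7 the ratio is 1.96 for follow-up values or 1.18 for changes. The correlations are assumptions.

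For the primary, the gain depends on how many class I patients enrol, which the article does not give. With an assumed 10% to 30%, stratification raises power from about 71% to 85% at the low end and from about 41% to 75% at the high end. With none there is no material difference.

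This is an improvement available at no cost. It is not an error that would invalidate the trial.

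**What to change.** Amend section 2.9 before any unblinded analysis:

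- **6MWT, BNP, LVEF, SF-36:** estimate the between-arm difference at week 24 by ANCOVA, or an equivalent baseline-adjusted model, with the baseline value as covariate. Report it with a 95% confidence interval.
- **Primary response rate:** use a Mantel-Haenszel test and risk difference stratified by baseline NYHA class. A class I stratum without responders causes no difficulty here, whereas a class I term in a logistic model would not be estimable.
- **Within-arm changes:** report descriptively, with no p-values and no efficacy claim.

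The cost is a few lines of wording. Baseline values and NYHA class are already collected, so no extra patients, visits or measurements are needed.
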